### Recruitment, screening, and enrollment

#### Prenatal practices

Prenatal care practices will be recruited using existing networks of the study investigators and members of the study external advisory board. Recruitment information will include a link to an interest survey. Any practices that indicate an interest in study participation will be contacted by study staff. If eligible, additional information will be collected from the selected practices for covariate constrained cluster randomization. In addition, to facilitate intervention implementation, each prenatal care practice will be asked to nominate a site champion for participation in the overall Study Advisory Board (SAB). The SAB will meet with study staff during the active implementation period. During these virtual meetings, suggestions or concerns may be discussed including recruitment strategy, recruitment and retention statistics, implementation challenges and solutions, and other lessons learned. To resolve any practice-specific challenges, study staff will meet with the site champions in one-on-one meetings.

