### Description of the intervention

The ADEPT intervention components are described in accordance with the template for intervention description and replication (TiDieR) checklist (**S2 File**) [20]. The core and adaptive components of ADEPT are shown in **Fig 2**. The core component of ADEPT is a prenatal provider recommendation in favor of maternal and childhood vaccinations. Adaptive components include a multimedia educational website and phone consultations with a vaccine navigator. These components are described below.

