#### Cluster-Randomized Trial (CRT)

We will cluster-randomize 14 study practices in a 1:1 ratio to the intervention or control arm utilizing a covariate constrained randomization approach [23]. Practices in the intervention arm will implement the standard of care plus ADEPT whereas practices in the control arm will continue to implement the standard of care (no ADEPT, **Fig 3**). After the PIs in the intervention and control arms give birth, we will assess timeliness of the 2-month vaccines for the child using data from the state immunization registry. The primary study outcome will be the difference between the intervention and control arms in the timeliness of childhood vaccinations recommended for children at 2 months (see **Outcomes**).

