### Participants and eligibility criteria

The prenatal practices will be those based in North Carolina and who provide routine prenatal care to PIs. Childhood vaccination discussions with PIs should not be part of practice standard of care for eligibility.

Prenatal providers will include those working in intervention practices. There are no exclusions by provider type or training.

PIs will be first-time pregnant individuals who receive routine prenatal care in study practices. PIs who are at a high risk of preterm delivery will be excluded to ensure there is adequate time to deliver the adaptive intervention components. High risk pregnancy will include multiple pregnancy, known fetal congenital malformations or genetic abnormalities, or documented as at-risk by the prenatal provider. Due to the timing of the ADEPT core component, PIs will be in their late second trimester during intervention exposure. For the NMM, vaccine hesitant PIs who are at least 18 years of age, provide informed consent for enrolment in NMM, and plan to stay in the study area for at least 3 months after delivery, will be eligible.

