### Statistical considerations

#### Sample sizes

*Provider trainings*. Only individuals from the intervention practices will be offered access to the trainings. All providers, staff and trainees at these practices will be eligible to participate in the training.

*CRT*. We anticipate the proportion of children who receive delayed or no vaccination at 2 months of age at baseline to be 20% [6]. We estimate that the intervention will reduce this proportion to 10%. We used a sample size formula for a two-sided Z-test comparing two proportions that accounts for the CRT design and incorporates a small-sample bias correction suitable for CRTs with fewer than 30–40 clusters in total (see equation (3) of Thomson et al, and more details in **S5 File**) [27]. With a sample size of 7 practices in each arm (14 total) and with at least 55 PIs/practice (770 total) the study would be powered at 90% to detect a difference in the proportion of 10% between arms at a two-sided alpha level of 5%, assuming that the coefficient of variation of cluster (i.e., practice-level) proportions with the primary outcome is 0.15 [27]. The target sample size is further inflated by 10% (total: 850) to accommodate a small reduction in power anticipated due to variable enrollment by practice and a small proportion of children with missing effectiveness outcomes due to out-of-state movement [28, 29]. In reality, the sample size for each practice will depend on practice size and eligibility of the PI population seen during the study period. Given that the primary outcome will be measured via data linkage of practice-level data to the state immunization registry using an honest broker, we will request an extract of data for all eligible PIs who are seen at the practice during the study period with the goal that the majority of enrolled practices would be expected to meet this target. Sensitivity analyses show that 80% power would be achieved if the proportion of children who delayed or refused vaccination at 2 months of age is 30% (rather than 20%) with a slightly smaller CV of 0.125 or even if the coefficient of variation is as large as 0.2 (**S5 File**).

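### As worded, control practices may sit on the same advisory board that discusses how ADEPT is being delivered, an avoidable contamination risk that would pull the primary effect toward no difference

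*Protocol article*

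**What the plan says.** Under Prenatal practices, directly after describing the data collected for constrained randomization, the article states, with the declared purpose of helping the intervention to be implemented, that "each prenatal care practice will be asked to nominate a site champion for participation in the overall Study Advisory Board (SAB"). On timing it says: "The SAB will meet with study staff during the active implementation period". On content, at these virtual meetings "suggestions or concerns may be discussed including recruitment strategy, recruitment and retention statistics, implementation challenges and solutions, and other lessons learned". Challenges specific to one practice go to one-on-one meetings between study staff and the champion.

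Four other statements define the contrast between arms:

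- Cluster-Randomized Trial: "practices in the control arm will continue to implement the standard of care (no ADEPT").
- Participants and eligibility criteria: "Childhood vaccination discussions with PIs should not be part of practice standard of care for eligibility".
- Description of the intervention: "The core component of ADEPT is a prenatal provider recommendation in favor of maternal and childhood vaccinations".
- Sample sizes: "Only individuals from the intervention practices will be offered access to the trainings".

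**The concern.** The trial tests whether adding a prenatal conversation about childhood vaccines changes what happens at 2 months. It therefore recruits practices that do not hold such conversations and withholds the training from half of them. The advisory board provision, followed literally, brings one representative of every practice into a shared forum during delivery, where those conversations may be discussed.

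The core component is something a clinician says. It needs no website, navigator or questionnaire, so it is the part of ADEPT most easily picked up by hearing about it. If some control practices began doing so, fewer control-arm children would be vaccinated late or not at all. The estimated effect would shrink and power would fall. The study's own procedure would open this route, and it is easily closed.

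**Working it through.** **Step 1: who is on the board?** The two readings compare as follows.

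- *For all practices:* the sentence says *each* practice and an *overall* board. It stands in the practice-recruitment section, next to the pre-randomization data collection. Elsewhere the article names the intervention practices when it means only those: in the eligibility text for providers, in the recruitment of providers, in the provider interviews, and in access to training. Here it does not.
- *For intervention practices only:* the stated purpose is to facilitate implementation, and control practices implement nothing. Recruitment and retention statistics fit the nested mixed methods study best, and that study recruits only in the intervention arm.

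The text leaves both readings open.

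**Step 2: is there a safeguard elsewhere?** The 10% inflation of the sample size is assigned to variable enrollment and out-of-state movement. The limitations section discusses self-selection into the nested study, covariate imbalance, early delivery and variable recruitment. Neither names contamination.

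**Step 3: what could it cost?** Inputs from Sample sizes: delayed or no vaccination p0 = 0.20 (control) and p1 = 0.10 (intervention); m = 55 per practice; c = 7 practices per arm; coefficient of variation k = 0.15; two-sided alpha 5%. S5 File, which gives the formula in detail, is not shown. I assumed the usual cluster-trial formula for two proportions, with one added cluster per arm as the small-sample correction:

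- V = p0(1 − p0)/m + p1(1 − p1)/m + k²(p0² + p1²)
- c = 1 + (1.96 + z_power)² × V / (p0 − p1)²
- power = Φ( |p0 − p1| × √((c − 1)/V) − 1.96 )

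*The plan's own figure:* V = 0.16/55 + 0.09/55 + 0.0225 × 0.05 = 0.002909 + 0.001636 + 0.001125 = 0.005670. For 90% power, c = 1 + 10.507 × 0.005670/0.01 = 6.96, that is, 7 per arm. Power at c = 7 is Φ(0.10 × √(6/0.005670) − 1.96) = Φ(1.293) = 90.2%. This reproduces the stated 90%.

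*Illustration, intervention arm held at 10%* (the control-arm falls are assumptions; the article gives none):

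| Control rate | Difference | V | Power |
|---|---|---|---|
| 20% | 10 points | 0.005670 | Φ(1.293) = 90.2% |
| 19% | 9 points | 0.005472 | Φ(1.020) = 84.6% |
| 18% | 8 points | 0.005274 | Φ(0.738) = 77.0% |

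Power passes below 80% somewhere between a control rate of 18.5% (81.1%) and 18% (77.0%), that is, once the control arm has taken up between 15% and 20% of the planned effect.

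**Step 4: how demanding are those falls?** With seven control practices of equal size, a 1-point fall in the arm mean requires 7 × 1 = 7 practice-points. If only two practices changed, each would have to fall by 7/2 = 3.5 points. A 2-point fall would require 14/2 = 7 points in each, or 70% of the planned 10-point effect, in practices without training or the adaptive components. The second scenario is therefore a severe one unless uptake is spread over more practices.

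**The case against.** The strongest reply is that the paragraph, read as a whole, describes support for practices that deliver ADEPT. The purpose clause, the timing and most of the topics fit that reading, and the composition of an advisory board is operational detail that an article may leave to the full protocol. This has weight: it is not established that control practices sit on the board. But the article does more than stay silent. It states a procedure for each practice without limit by arm, and staff who followed it literally would invite control practices.

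A reader might go further and infer that the control arm is exposed to the intervention. The documents do not support that. Practices will only be asked to nominate, and the topics are ones that may come up. Training is expressly closed to control practices, and nothing gives them the screening questionnaire, the website or the navigator. Hearing about delivery is not receiving ADEPT. Nor does the article describe champions as opinion leaders, so it offers no basis for predicting how far one champion would change a practice.

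It is also fair to say that the power figures show only what a smaller difference would cost, and that any bias would be conservative. Both points stand and limit the seriousness of the issue. They do not justify leaving the route open.

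**Conclusion.** The point holds as a risk of contamination, conditional on control practices taking part in the board, which the wording allows but does not settle. The part most plausibly affected is the core provider recommendation. The effect would be dilution of the primary contrast and loss of power, with no inflation of type I error.

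The size is unknown. The fall from 90% to about 85% or 77% rests on assumed control rates of 19% and 18%, on an unchanged intervention rate of 10%, on the plan's coefficient of variation and cluster size, and on a formula inferred from its description that reproduces the stated power. It is not a forecast. The change is worth making because it is cheap and protects the primary contrast under either reading of the sentence.

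**What to change.** State in the protocol which practices sit on the Study Advisory Board. Limit membership, or at least every meeting with implementation content, to champions from intervention practices. Keep contact with control-arm champions to data extraction and logistics until the control-arm exposure window has closed, through separate calls or the one-on-one meetings the article already provides for. Share lessons learned with control practices after that.

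The cost is a sentence in the protocol and a short separate set of calls. The downside is that practices in different arms cannot exchange experience during the trial.

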#### Prenatal providers

All prenatal providers and staff at prenatal practices randomized to the intervention arm will be eligible to participate in the provider training. For those individuals who provide informed consent, we will collect information on their characteristics (e.g., demographics, prior training, years in practice) and their feedback on training sessions. A subset of the providers will be invited to participate in in-depth interviews to discuss their experience making childhood vaccine recommendations to PIs.

#### PIs

We will seek a waiver of consent for the assessment of the study outcomes among PIs and their children in the CRT since outcome data will be extracted from the state immunization registry where they are routinely reported, and any identifying information will be managed by an honest broker who is independent from the study team. Vaccination outcomes will be assessed at the practice-level and compared between study arms. Recruitment for the NMM study will occur in the intervention arm among those who self-identify as vaccine hesitant per the screening questionnaire. PIs who are eligible for the NMM study will be contacted by study staff and only those who provide informed consent will be enrolled in the NMM study. Participation in the NMM study is voluntary; PIs who do not want to participate will still have access to the ADEPT adaptive components as part of the CRT. Trained study staff will conduct the informed consent process in person or over the phone, with an electronic signature documenting consent. For the qualitative portion of the NMM study, PIs will be selected for the interview at the time of the endline survey (2 months post birth) to include perspectives from those who vaccinated their children on time, as well as those who delayed or refused vaccines at 2 months, according to CDC’s Birth-18 years immunization schedule (**S4 File**).

### Data collection

#### Provider trainings

Quantitative and qualitative data will be collected as a part of the provider training. Post-training evaluation surveys will capture feedback on training sessions, including the format of training, and delivery. Evaluation surveys will be self-administered by the providers after each of the four training sessions. All providers who complete the trainings, regardless of participation in post-training evaluations, will be eligible for continuing medical education (CME) credits, including Maintenance of Certification (MOC) Part 4 credits from American Board of Obstetrics and Gynecology (ABOG) [25]. After the trainings have been completed, interviews will be conducted with a subset of 12 prenatal providers from intervention practices to assess any additional training needs and to better understand the experience of implementing vaccine recommendations in practice. These interviews may be completed in-person or virtually and will be conducted in English by a trained interviewer. Each interview is expected to last approximately 15 minutes and will be audio-recorded for transcription and analysis purposes.

#### CRT

Representatives from each practice will complete a survey to provide data on the practice-level covariates necessary for constrained randomization and to assess readiness for implementation of ADEPT. At the time of outcome assessment, study practices will utilize medical records to generate a list of first-time PIs who were in their second and third trimester during the study period. The linkage of these data to the state immunization registry will be used to determine vaccination outcomes for children post-delivery. Identifiable data will be managed by an honest broker who will communicate with the state immunization registry for receiving vaccination data. De-identified datasets will be shared with the study team by the honest broker for calculation of vaccination outcomes.

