#### Core component

The core component of ADEPT is a vaccine recommendation by prenatal providers to first-time PIs at the end of the second trimester (26–32 weeks), encouraging vaccinations during pregnancy and for their child after birth. Prior to intervention implementation, providers at intervention sites will complete four training sessions on the following topics: overview of the routine vaccination program in the US (including COVID-19 vaccine and RSV immunization recommendations), vaccine clinical trials and safety, and strategies for effective communication (2 sessions). During active implementation, prenatal providers will make recommendations encouraging timely maternal and childhood vaccinations.

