#### CRT

Summary characteristics for study practices will be described by intervention and control arm. We will also describe the distribution of vaccination intention among PIs. A timeframe of 28 days from the vaccination due date will be used as the window of timeliness. Timely vaccination doses will receive a score of 2, doses that are delayed beyond the 28-day window will receive a score of 1, and the non-receipt of a dose during outcome assessment will be scored a 0. For the time point of outcome determination (2 months), we will create a cumulative timeliness score and use that to determine the proportion of children who receive all recommended vaccines in a timely fashion. For the analysis of the primary outcome of vaccination timeliness, we will use data on vaccination outcomes for children of all PIs enrolled in the study (including those who screened as vaccine-hesitant in the intervention arm). The generalized estimating equations (GEE) approach will be used to account for clustering of outcomes due to the hierarchical structure of data (PIs nested within practice). The child-level binary outcome (timely vs. not) will be regressed on an intervention-arm indicator, strata and the practice-level covariates used in the covariate constrained randomization procedure. We note that no additional adjustment by individual-level characteristics is possible due to the source of data, i.e., state immunization registry. Log and identity links will be used to obtain both relative and absolute intervention effects, as per recommendations from the CONSORT statement on trial reporting [22]. Robust standard errors will be used together with finite-sample corrections to reduce inflated Type I error rate, which is expected due to the small numbers of clusters (I.e. 14 practices) [33]. Given that outcomes are obtained from the state immunization registry, we do not expect missing data in the usual sense. Instead, some outcome data will not be available for those children whose birthing parents were enrolled towards the end of the study. Since this is by design, the missing data is not expected to bias the estimated intervention effect. A similar GEE approach will be used to model vaccination coverage.

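### The trial's outcome list is drawn by trimester within an undefined study period, not by the 26–32-week ADEPT window; on one reading this dilutes the primary effect

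*Protocol article*

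**What the plan says.** **Exposure.** Under Core component, the provider recommendation is given at 26–32 weeks, during active implementation and after the providers have been trained. Participants and eligibility criteria adds: "Due to the timing of the ADEPT core component, PIs will be in their late second trimester during intervention exposure". That sentence describes timing. It is not an entry criterion, and the section sets no gestational-age limit.

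**Outcome population.** Three sections describe it in different terms:
- Data collection, CRT: practices use medical records to "generate a list of first-time PIs who were in their second and third trimester during the study period".
- Sample sizes, CRT: "we will request an extract of data for all eligible PIs who are seen at the practice during the study period".
- Data analysis, CRT: the primary analysis uses outcomes for "children of all PIs enrolled in the study".

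None of the three refers to the 26–32-week window or to active implementation. The study period is not dated for PIs.

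**Late entrants.** Data analysis, CRT also says that "some outcome data will not be available for those children whose birthing parents were enrolled towards the end of the study" and treats this as a feature of the design.

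**Size.** 7 practices per arm with at least 55 PIs each (770 in total) give 90% power for 20% against 10% delayed or unvaccinated, with a coefficient of variation of 0.15 and two-sided alpha of 5%. The total is raised by 10% to 850 for variable enrolment and children who move out of state.

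**The concern.** The people who can receive ADEPT and the people whose children are counted are fixed by different rules. A PI already past 32 weeks when a practice begins, or not yet at 26 weeks when it stops, cannot receive the core component at the planned time. If such PIs are counted, the intervention-arm rate moves towards the control rate and the 10-point difference shrinks. The 10% inflation was not set aside for this.

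The list will be produced from medical records at 14 practices, so a rule that can be read in two ways can also be applied in two ways.

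**Working it through.** **1. Reproduce the stated power.** The cited equation is not shown. I assumed the usual formula for comparing two proportions in a cluster trial, with one cluster per arm added as the small-sample correction:

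V = [p0(1−p0) + p1(1−p1)]/m + k²(p0² + p1²)

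clusters per arm = 1 + (1.96 + 1.28)² × V/(p0−p1)²

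power = Φ(√[(7−1)(p0−p1)²/V] − 1.96)

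With p0 = 0.20, p1 = 0.10, m = 55 and k = 0.15:
- V = 0.25/55 + 0.0225 × 0.05 = 0.00567.
- Clusters per arm = 6.96, so 7.
- Power at 7 per arm = 90.2%.

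The plan's 90% is reproduced.

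**2. Narrow reading: both trimesters within the period.** Taking the boundary at about week 28 (an assumption), each listed PI crosses it inside the period and so is in the 26–32-week window at that time. The unexposable share is about 0 and the 90% stands. A PI already at about 28–32 weeks at the start can be exposed but is not listed.

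**3. Inclusive reading: any time in the second or third trimester.** Assume steady entry, trimesters two and three as weeks 14–40, and a period of T weeks.
- Listed PIs are proportional to T + 26.
- PIs who touch weeks 26–32 during the period are proportional to T + 6.
- The difference, 20, is made up of 8 (weeks 32–40 at the start) and 12 (weeks 14–26 at the close).
- If the group of 12 drops out for lack of outcomes, the unexposable share is f = 8/(T + 14).
- If it is retained, f = 20/(T + 26).

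**4. Effect on power.** With no effect in the unexposable share, p1 = 0.10(1−f) + 0.20f and the difference is 10(1−f) points. The lower power figure fixes the list at 55 per practice. The higher one lets unexposable PIs come on top of 55 exposable ones, so m = 55/(1−f).

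| T (weeks) | f, end group dropped | Difference (points) | Power | f, end group retained | Power |
|---|---|---|---|---|---|
| 26 | 20% | 8.0 | 71–78% | 38% | 47–62% |
| 52 | 12% | 8.8 | 80–84% | 26% | 64–74% |
| 104 | 7% | 9.3 | 85–87% | 15% | 77–82% |

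Worked case, T = 52 with the end group dropped: f = 8/66 = 0.121, p1 = 0.112 and the difference is 0.088. At m = 55, V = 0.00590 and power is 80.0%. At m = 62.6, V = 0.00533 and power is 83.9%.

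**5. Threshold.** Power falls below 80% at f of about 12% with 55 listed per practice, or about 18% if the unexposable PIs are additional.

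**6. The inflation.** Even if all of it were available for this purpose (850/14 = 60.7 per practice), power would be 83% at f = 12% and 75% at f = 20%.

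**The case against.** The strongest reply is that the data collection text joins the two trimesters with *and*. Read literally, this puts every listed PI in the exposure window. The sample size section limits the extract to eligible PIs and states no gestational age, so it does not expressly contradict that reading. The eligibility section links PIs to the timing of the core component. This stands as far as it goes: the narrow reading is available, and on it dilution is near nil. But the request for all eligible PIs seen in the period does not carry the both-trimesters condition, and eligibility has no gestational-age rule to supply it. The narrow reading also leaves out some PIs who can be exposed.

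Two further replies stand. The analysis section expects late entrants to lack outcomes, which removes much of the group under 26 weeks at the close, so the smaller shares are the safer ones. And the length of the period is not given, so no single figure can be fixed.

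A reader might also infer that the three descriptions are three different denominators yielding three primary results. The documents do not show this: one describes how the list is made, one the data request and one the analysis set, and they may be loose accounts of a single population. The word *enrolled* is imprecise for a trial that seeks a waiver of consent, but it does not by itself define another set.

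**Conclusion.** The point holds as a definition that needs tightening: should fix, moderate confidence. The outcome population is not tied to the exposure window, and a permissible reading counts PIs who could not have been exposed.

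On that reading, with the end-of-period group lacking outcomes, the unexposable share is about 20%, 12% or 7% for periods of 26, 52 or 104 weeks. Power is then about 71–78%, 80–84% or 85–87% against the stated 90%. It is lower if the end-of-period group is retained. These figures rest on steady entry, weeks 14–40, no effect in unexposable PIs, and the assumed sample size formula.

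It would be tempting to conclude that the 90% power is not delivered. The document does not support that unconditionally, because the narrow reading leaves the power intact and the period length is unstated. Nor is this a bias towards a false positive: the same list rule applies in both arms, so the consequence is attenuation and lost power.

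**What to change.** Use one definition in the data collection, sample size and analysis sections: eligible first-time PIs under care at the practice whose 26–32-week window fell within the active implementation period, whether or not ADEPT was delivered. Ignoring actual receipt keeps the comparison as randomised. Apply the same calendar window to control practices, and state its dates before the data request is issued. Then recheck the target of 55 per practice on this population.

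The cost is a change of wording in the protocol and the data request. The downside is that somewhat fewer children per practice may qualify, so a practice near the target may need a longer window.
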